### Setting and participants

The study will be implemented on *n* = 28 acute wards (=clusters) in seven psychiatric hospitals in the greater Munich area. Eligibility criteria for the wards to be included are: acute psychiatric ward in one of the participating hospitals, patients with psychiatric disorders are commonly treated on these wards.

All patients treated on these wards and on admission to the ward, each patient fulfilling the inclusion criteria will be consecutively offered participation in the trial.

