#### Randomization and blinding

We will determine pairs of comparable wards (number of patients, distribution of diagnoses, staff etc.) and then randomize one ward of each pair to the intervention and one ward to the control condition. While the principal investigators will determine the paired wards, the statistical institute of our department (IMedIS) will do the randomization.

Randomization takes place at cluster level (*n* = 14 wards each to the intervention group or control group) to minimize contamination effects [19].

As to the nature of the intervention (implementation of RTW-experts) there will be no blinding.

To avoid selection bias, all patients fulfilling inclusion criteria will be recruited consecutively in the intervention and control group. This process is monitored by the study center and will be reported in form of a CONSORT diagram. There will be special emphasis on documenting how many patients (and for what reasons) did not consent to participate in the trial.

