### Sample size calculation and statistical analysis

The aim is to obtain a sample of *n* = 28 clusters (i.e. psychiatric acute wards) with a total of 200 patients (8–10 per cluster). For this, about 2000 patients need to be screened (Mernyi et al., 2018).

In order to be able to demonstrate a significant result with a power of 80% assuming a small to medium effect size (0.5), a total sample size of 128 patients is required (two-sided independent samples t-test, α = 0.05). With regard to expected drop-outs (drop-out rate 30–40%), this minimum number of cases is planned to be exceeded by 72 patients. Thus, a total of 200 patients are to be included (100 in each group).

The primary analysis will be a comparison of days in work at T4 between the intervention and control groups. To assess the effect of the intervention on the continuous primary outcome, a random effects linear regression model will be fitted with ward (cluster) as a random effect term and intervention group as a fixed effect. The point estimate for the intervention effect will be reported together with the corresponding 95% confidence interval. A *p*-value < 0.05 will be considered as providing statistical significant evidence of a group difference. A per protocol approach will be taken to the analysis, i.e. patients in intervention clusters will be analyzed in this group, if they had contact with the RTW-expert at least once during their inpatient stay and once after discharge.

Exploratory analyses will be performed to assess the effect of the intervention on the secondary outcome measures. Random effect linear models will be fitted to the continuous secondary outcome measures, analogous to the primary analysis. For binary secondary outcome measures, logistic regression models using GEEs will be fitted.

The health economic analysis is based on the net benefit approach. To analyze the cost-effectiveness of the RWT intervention, the incremental cost-effectiveness ratio (ICER) is determined for gaining a QALY compared to routine treatment. The estimation of ICER stochastic uncertainty is done by nonparametric bootstrapping and the determination of the cost-effectiveness acceptance curve [29].

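### With 14 wards per arm, the logistic GEEs for binary secondary outcomes need a small-sample correction: without one, common outcomes are tested at about 6.5–8% instead of 5%

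*Protocol article*

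**What the plan says.** The section on sample size and statistical analysis gives the method for binary secondary outcomes in one sentence: "For binary secondary outcome measures, logistic regression models using GEEs will be fitted". It sits in a paragraph that opens "Exploratory analyses will be performed to assess the effect of the intervention on the secondary outcome measures". The article does not name the variance estimator, the working correlation, the reference distribution or the degrees of freedom. It neither states nor rules out a small-sample correction.

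The number of clusters is fixed. Under Setting and participants the study runs on "28 acute wards (=clusters) in seven psychiatric hospitals". Under Randomization and blinding, "Randomization takes place at cluster level (*n* = 14 wards each to the intervention group or control group"), after comparable wards have been paired, the plan being to "randomize one ward of each pair to the intervention and one ward to the control condition".

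Termination and relapse are listed under Secondary outcomes without expected rates. The only rate for a binary work outcome is in the Background: up to 30% of working inpatients do not return to work. The abstract names the return rate as something to be evaluated.

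**The concern.** GEE inference normally rests on the sandwich variance and a normal reference, and both are justified for a large number of clusters. With 14 per arm, the residuals are measured around means that the same few wards determine, so the sandwich variance is biased downward. A normal quantile then ignores the uncertainty in a variance estimated from 28 ward totals. Both effects make p-values too small and intervals too short. An exploratory label lowers the stakes but does not make a nominal 95% interval cover 95% of the time. At stake is whether modest differences in common binary outcomes, such as the proportion returning to work, look more certain than they are.

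**Working it through.** The article gives no error rate or interval width for the GEE analyses, so there is no figure of its own to reproduce. Its sample size of 128 concerns the primary outcome and does not bear on this point.

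**Inputs from the article.** 28 wards, 14 per arm, in 14 pairs; 200 patients, i.e. 200/28 = 7.1 per ward; dropout of 30–40%, leaving 120–140 patients, or 4.3–5.0 per ward. I use 200 and 130.

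**Assumptions, not in the article.** Intraclass correlation 0.02–0.05 in the main runs; ward sizes equal, or varying with coefficient of variation 0.5; event rates 5–30%; independence working correlation.

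**Formulas.** With arm as the only covariate, let ward i have n_i patients and y_i events, in an arm with n patients and event proportion p. The arm's contribution to the variance of the log odds ratio is:

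- uncorrected sandwich: Σ(y_i − n_i p)² / [n p(1−p)]²
- Kauermann-Carroll: the same, with each squared term divided by (1 − n_i/n)

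**Rough answer by hand, equal ward sizes.** Here n_i/n = 1/14.

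1. Standard error ratio, corrected to uncorrected: 1/√(13/14) = 1.038.
2. Quantile ratio, t(26) to normal: 2.056/1.960 = 1.049.
3. Interval width ratio: 1.038 × 1.049 = 1.088. The uncorrected interval is therefore about 8% shorter (1/1.088 = 0.92).
4. The uncorrected test rejects when the corrected statistic exceeds 1.960 × √(13/14) = 1.889. If that statistic follows t(26), the error rate is P(|t| > 1.889) = 7.0%. The normal reference alone would give P(|t| > 1.960) = 6.1%.

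**Simulation under no effect.** Beta-binomial wards, 40,000 trials per setting, Monte Carlo standard error about 0.1 percentage points. The ranges cover both intraclass correlations and both ward-size patterns. Samples with no events in an arm are excluded (up to 11% of samples at a 5% event rate with 130 patients).

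| Event rate | Patients | Uncorrected, normal | Kauermann-Carroll, t(26) |
|---|---|---|---|
| 30% | 200 | 6.7–7.8% | 4.7–5.2% |
| 30% | 130 | 6.4–7.7% | 4.5–5.3% |
| 20% | 200 | 6.6–7.6% | 4.6–5.2% |
| 20% | 130 | 6.3–7.4% | 4.3–5.1% |
| 10% | 200 | 6.4–7.5% | 4.3–5.0% |
| 10% | 130 | 5.0–6.1% | 2.9–3.5% |
| 5% | 200 | 3.8–4.9% | 2.1–2.6% |
| 5% | 130 | 1.2–2.4% | 0.4–1.0% |

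Corrected intervals are 9% wider with equal ward sizes and about 10% wider with unequal ones.

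**Effect of pairing.** These runs used logit-normal ward effects, event rates of 20% and 70%, latent intraclass correlation 0.05–0.20 and unequal ward sizes, and the GEE ignored the pairs. The uncorrected test rejects:

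- 7.0–8.1% if pairing explains none of the between-ward variance
- 5.0–6.6% if it explains half
- 2.2–5.9% if it explains all

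**Effect of the working correlation.** These were smaller runs of 1,000–1,500 trials with an exchangeable structure, at a 70% event rate and intraclass correlation 0.05. The uncorrected test rejects 5.7% with equal ward sizes and 8.6–10.3% with unequal ones. One run at a 10% event rate with 130 patients and unequal wards gave 8.5%. A run at 5% was unstable because of separation and is not used.

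**The case against.** The strongest objection is that the article never chooses the uncorrected sandwich. It names GEE and stops. Variance estimator and degrees of freedom are details that a condensed article leaves to the full protocol or analysis plan, and a corrected GEE fits the printed sentence unchanged. This stands, and it makes the point conditional: a reader might infer that the plan has committed to the uncorrected variance, but the text does not say so. What remains is that the article fixes a method whose default inference does not suit the 28 wards that it also fixes.

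A reader might also infer that every binary secondary outcome, including termination and relapse, would be reported with intervals that are too short. The documents do not support that. Near a 5% event rate the uncorrected test under independence rejects below nominal, and the article gives no rate for either outcome.

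Pairing can offset the inflation, and matching on patient numbers, diagnoses and staff may well explain some ward variance. With half explained, the error rate is about 6%. Rates clearly below nominal appeared only when it explained all of it. The share is unknown, so the offset cannot be relied on.

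Finally, the sentences on the 95% interval and the 0.05 threshold belong to the primary analysis, and no confirmatory claim rests on the binary outcomes. That is right, and it keeps the severity low.

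**Conclusion.** The concern holds as a minor, conditional point. If no small-sample correction is specified elsewhere, the GEE analyses of common binary outcomes (event rate about 20% or more) run at about 6.5–8% type I error under independence working correlation, and at about 6% if pairing explains half the between-ward variance. An exchangeable structure with unequal ward sizes may do worse, on smaller simulations. A return-to-work proportion near the 70% implied by the Background would fall in the affected range. For rare outcomes (about 5%) no inflation was found under independence, and for termination and relapse the direction cannot be stated. The intraclass correlations, ward-size variation, event rates and share of variance explained by pairing are all assumptions.

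**What to change.** Keep the logistic GEE and add one sentence to the analysis plan, if it is not already there: standard errors use a small-sample corrected variance (Kauermann-Carroll or Fay-Graubard), with tests and intervals referred to a t distribution on the number of wards minus 2, i.e. 26 degrees of freedom, or fewer if ward pair is in the model. The figures above are for Kauermann-Carroll.

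The cost is a software option. Intervals become about 10% wider. The test becomes conservative for events at or below about 10%, most clearly with about 130 patients analysed (2.9–3.5% at a 10% event rate).

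I would not replace the GEE with a logistic mixed model for this purpose. It targets a ward-conditional odds ratio in place of the population-averaged one, and its behaviour here was not tested.

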**Fig. 1 Fig1:**
[figure not shown]
German terms and their translation: BEM = Betriebliches Eingliederungsmanagement (Corporate integration management), Stufenweise Wiedereingliederung (gradual reintegration)

We expect improvements in the number of patients who will be able to return to work and also in the number of days at work in the year after release from hospital. This could also result in substantial economic savings (for example, sickness benefit, loss of productivity, etc.). Mediators of these expected improvements are increased numbers of patients for whom specific supportive measures (e.g., work therapy, gradual reintegration, BEM processes, etc.) are initiated. We assume that the proposed intervention primarily will increase the implementation of measures already existing in routine care and will help to overcome the interface problem at the time of inpatient discharge.

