### Intervention and control condition

The intervention consists of the implementation of Return to Work experts in the participating acute care units. The RTW experts (social workers, who in the framework of the RETURN study are added to existing resources) support patients and mental health care professionals on the wards in all areas related to the possible return of patients to their workplace. The RTW experts will thereby act as case managers, who usually first clarify the specific needs of the clients (i.e. participating patients who might return to an existing workplace), subsequently communicate these needs to all people involved in the treatment process and initiate and accompany a corresponding treatment path. The services of the RTW expert can be claimed by the patients for up to half a year. In order to guarantee a minimum of intervention, it is planned that the RTW experts meet at least twice – one appointment during the inpatient stay and one after release. A maximum of intervention is not defined. Above all, existing support services (e.g. work therapy, cognitive training, socio-educational counseling, etc.) should be activated for the individual patient. However, if there is a limitation of resources, more specific needs or issues (for example, discussions with the patient’s employer, Integration Services, etc.), the RTW expert can also take personal action and support the patients accordingly. In addition, the RTW expert is to be active at the interface between discharge and reintegration and to assist the patient even after discharge in the activation of occupational and outpatient psychiatric-psychotherapeutic support measures. The RTW experts thus assume the function of a job-related discharge management.

The approach of the RTW experts is guideline-based. The RTW experts will be specifically trained. For this purpose, a guideline and a training program for the RTW experts has been established together with the Advisory Board in the first project phase (Kohl et al. in preparation), and will be evaluated within the framework of the study and then revised if necessary, so that the guideline and RTW expert training can be published at the end of the project.

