### Data collection

The same data at the same time points will be collected in the intervention and control group (Table 1). Data collection will take place at five times during the inpatient stay and after discharge.

**Table 1 Tab1:** Planned data collection

	T0 (shortly after admission to hospital)	T1 (shortly before release from hospital)	T2 (3 months after release)	T3 (6months after release)	T4 (12 months after release)
Patient					
Demographics including information on					
School and vocational training	x				
Employment relationsship	x				
Business, enterprise (industry)	x				
Business, enterprise (size)	x				
Motivation	x	x	x	x	x
Anxiety, confidence	x	x			
Days of incapacity to work	x		x	x	x
COPSOQ	x			x	
COPSOQ (additional information)	x				
Self-stigma of mental illness scale short form – self-concurrence	x	x		x	
Cognitive appraisal of stigma-related stress	x	x		x	
Questions concerning disclosure of the disease at the workplace including					
Questions on the decision-making phase	x	x		x	
Questions on the decision to disclose	x	x		x	
Questions on the attitude towards disclosure	x	x		x	
Decisional Conflict scale	x	x		x	
Cognitive performance level		x			
CSSRI	x	x	x	x	x
Preparation of the return through the hospital		x			
Preparation of the return through the employer		x			
Preparation of the return through the RTW expert (intervention group only)		x		x	
Questions on the existing help network		x		x	x
Content of the employer support				x	
Evaluation of the employer support				x	
Evaluation of the RTW expert support (intervention group only)				x	
EuroQOL - Gesundheitsbarometer	x	x		x	
EQ-5D		x		x	x
Self-efficacy expectation (RTW-SE)		x			
Resilience (RS-13)					x
Patient Health Questionnaire (PHQ-D)		x			
Days at work			x	x	x
Days of incapacity for work			x	x	x
Days of partial return to work			x	x	x
Questions on discrimination at the workplace				x	
Coping				x	
Attending physician					
CGI	x	x			x
GAF	x	x			x
ICD Diagnosis and medical history	x	x			x
HoNOS		x			
Prediction on return to work		x			
RTW expert (intervention group only)					
Type and scope of workplace-related support		x		x	
Evaluation of workplace-related support		x		x	
Prediction on return to work		x			
Quality of relationship		x		x	
Return to work				x	
Questions concerning the use of communication media				x	
Open summary				x	

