#### Secondary outcomes

As outlined above an improved return to work following an in-patient psychiatric care treatment of patients may also result in a shorter period of **time to return to work** (partial/full), lower **termination rates** (both sides), a higher **quality of life** (EQ-5D, [20]), a higher **social functional level** (Mini-ICF-APP, [21]; Global Assessment of Functioning (GAF), [22]), a higher **job satisfaction** (German version of the Copenhagen psychosocial questionnaire (COPSOQ), [23]), a different **perception of stigmatization** (Self-stigma of mental illness scale – short form – subscale self-concurrence, [24]; Cognitive appraisal of stigma-related stress, [25]), lower **decisional conflict in regard to disclosure of the mental illness** (Decisional conflict Scale, [26]) and probable reduced **relapse rates**.

The basis for estimating the **cost of the illness** and the **health economic evaluation** of the RTW intervention are the medical and psychosocial health services made use of by the subjects and the number of days of incapacity for work for the whole study period.

The days of incapacity to work of the patients are on the one hand directly requested by the patients and their practitioners. It is envisaged that the patient’s details will be checked against those of some health insurance companies in order to assess the extent to which the data match.

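### EQ-5D is not collected at the 3-month contact, so a QALY gain from earlier return to work may be partly missed in the ICER; the absolute amount is small

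*Protocol article*

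**What the plan says.** The protocol article, under Sample size calculation and statistical analysis, plans a net benefit analysis in which "the incremental cost-effectiveness ratio (ICER) is determined for gaining a QALY compared to routine treatment", with bootstrapping and an acceptability curve. It does not say how QALYs are formed from the EQ-5D values.

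Table 1 under Data collection fixes the schedule:

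| Instrument | T0 | T1 | T2 | T3 | T4 |
|---|---|---|---|---|---|
| EQ-5D | | x | | x | x |
| EuroQOL barometer | x | x | | x | |
| CSSRI (service use) | x | x | x | x | x |
| Days at work | | | x | x | x |

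T2 is the contact headed "T2 (3 months after release". The health barometer row ("EuroQOL - Gesundheitsbarometer x x x") is also blank at T2, so it does not fill the gap. The rows for incapacity days are marked at T2, as is the row "Days at work x x x".

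On the support itself, Intervention and control condition says: "The services of the RTW expert can be claimed by the patients for up to half a year". The minimum is "one appointment during the inpatient stay and one after release". The start of the half-year is not defined.

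Secondary outcomes states that better return "may also result in a shorter period of" time to return to work, partial or full. The text below Fig. 1 also expects "improvements in the number of patients who will be able to return to work", and more days at work over the year.

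**The concern.** A QALY is the area under a utility curve. With values only at discharge, month 6 and month 12, the first half-year of that curve has two end points and nothing between them. Most of the post-discharge support falls in this half-year, and a shorter time to return would show there first.

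If intervention patients return earlier and control patients follow, the between-arm difference in utility rises early and then narrows. A straight line from T1 to T3 cuts off whatever lies above it. The denominator of the ICER is then too small. Incremental net benefit falls at any positive value placed on a QALY, and the ICER rises if the intervention costs more.

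A later analysis plan cannot repair this, because it cannot supply a utility that was never asked. Service use and work days, by contrast, are asked at month 3.

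**Working it through.** The documents state no QALY or ICER figure, so there is none to reproduce. The check compares two schedules under assumed trajectories.

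**Inputs from the protocol article.** EQ-5D at 0, 6 and 12 months after release (T1, T3, T4); an existing contact at 3 months (T2). Up to 30% of working inpatients did not return (section on acute psychiatric crises), which is the basis for a 70% return plateau.

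**Assumptions, not in the documents.** Linear interpolation; utility rises by 0.10 on return to work; exponential times to return with medians m_I (intervention) and m_C (control), in months.

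**Formulas.** With D(t) the between-arm difference in mean utility and D(0) = 0:

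- D(t) = 0.10 × 0.70 × (0.5^(t/m_C) − 0.5^(t/m_I))
- True gain = (1/12) × integral of D from 0 to 12 months
- Planned schedule = 0.50·D(6) + 0.25·D(12)
- With T2 = 0.25·D(3) + 0.375·D(6) + 0.25·D(12)
- Area gained by adding T2 = 0.25·(D(3) − D(6)/2)

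The last line shows when the gap matters: only if the difference at month 3 departs from half the difference at month 6.

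**One case in full, medians 1 and 2 months.** D(3) = 0.0160, D(6) = 0.0077, D(12) = 0.0011.
- Planned: 0.50 × 0.0077 + 0.25 × 0.0011 = 0.0041
- With T2: 0.25 × 0.0160 + 0.375 × 0.0077 + 0.25 × 0.0011 = 0.0071
- True: 0.0082

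**Timing gain only, 70% return in both arms.**

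| Medians (intervention vs control) | True | Planned | Captured | With T2 | Captured | Missed as planned |
|---|---|---|---|---|---|---|
| 1 vs 2 | 0.0082 | 0.0041 | 50% | 0.0071 | 88% | 0.0041 |
| 1.5 vs 3 | 0.0111 | 0.0076 | 68% | 0.0103 | 93% | 0.0035 |
| 2 vs 4 | 0.0129 | 0.0099 | 77% | 0.0121 | 94% | 0.0030 |
| 2 vs 6 | 0.0213 | 0.0172 | 81% | 0.0201 | 95% | 0.0041 |

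Multiplied by 365, the missed amounts are about 1.1 to 1.5 quality-adjusted days. With the cost difference held fixed, an ICER based on 50% or 81% of the gain is inflated by 1/0.50 = 2.0 or 1/0.81 = 1.2.

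**More patients returning** (80% vs 70%, each plateau in place of the common 0.70).
- Same speed, median 3 months in both arms: planned schedule captures 92%, with T2 97%.
- Medians 2 vs 3 months: 82% and 95%.

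**Other shapes, for a gain d at month 3.** The share of the four-point area that the three-point curve misses:

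| Shape | Missed |
|---|---|
| Gone by month 6 | 100% (0.25d; 0.025 if d = 0.10) |
| Half left at 6, none at 12 | 43% |
| Half left at 6 and 12 | 33% |
| Held in full to 12 | 14% |
| Linear build-up to 6, then held | 0% |
| Only a quarter of the month-6 gain present at 3, then held | overcounted by 9% |

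**Step examples at +0.10.**
- Return at month 2 against month 5: true gain 0.10 × 3/12 = 0.025; the planned schedule records 0 and T2 recovers 0.025.
- Gain from month 1 until controls catch up by month 6: true 0.10 × 5/12 = 0.042; planned 0; with T2 0.025.

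**The case against.** The case against has five parts.

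- **Size relative to noise.** The shortfall is 0.003–0.004 QALY on assumed inputs. If the SD of 12-month QALYs were 0.15–0.20 (an assumption), then with 64 patients per arm (half of the planned minimum of 128) the standard error of the difference would be SD × √(2/64) = 0.027–0.035. The bias would be about 0.1 to 0.15 standard errors. This stands, and it limits the point's weight.
- **A stronger reading fails.** A reader might infer that the gain from earlier return is largely missed, or that the bias strikes exactly the effect the trial predicts. The documents support neither. A loss of the whole gain needs the arms to be equal again by month 6, and no section predicts that controls catch up. The article also expects more patients to return, more days at work, fewer terminations and probably fewer relapses. Such differences can last beyond month 6, where T3 and T4 measure them.
- **Interpolation is inferred.** An article may leave the QALY method to the full protocol or analysis plan, and work days at T2 could inform a model of utility. That is correct, but any such model would replace an observation that could have been made.
- **Timing of support is loose.** Support begins on the ward and the start of the half-year is undefined, so it cannot be equated with the interval from T1 to T3. It remains true that most post-discharge support falls there.
- **Different spacing is no contradiction.** Service use and work days accumulate over a period, and asking at T2 can serve recall; EQ-5D describes a point in time. This is right. The T2 rows show that the contact exists, not that the table is inconsistent.

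**Conclusion.** The point holds in a limited form. Table 1 leaves no utility observation between discharge and month 6 although the analysis needs QALYs and a 3-month contact takes place. If QALYs are interpolated linearly, a gain that comes early is understated, to the intervention's disadvantage. Under the assumed timing-only curves the planned schedule captures about 50–81% of it, against 88–95% with T2.

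The range across shapes is wide, from a complete loss if the arms have converged by month 6, through no loss with a linear build-up, to a slight overcount with a slow one. The documents give no utility trajectory to choose between these.

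The absolute amount is small, and the primary outcome is untouched. This is a cheap improvement worth making, not an error that invalidates the economic analysis.

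**What to change.** Mark EQ-5D at T2 in Table 1. Define the QALY for all patients as the area under T1, T2, T3 and T4:

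QALY = 0.125·u(T1) + 0.25·u(T2) + 0.375·u(T3) + 0.25·u(T4)

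The weights are the trapezoid weights for 0, 3, 6 and 12 months and sum to 1.

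For patients already past T2, treat the T2 utility as missing and impute it, with T2 work days among the predictors. One QALY definition then applies to everyone, and the main ICER does not depend on who happens to have a T2 value. Report the three-point curve as a sensitivity analysis.

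The cost is five more items at an existing contact and an amendment. Two limits remain. The imputation is only as good as the number of patients with an observed T2 utility. Four points still miss part of a short-lived gain: in the month 1 to 6 step example they recover 0.025 of 0.042. EQ-5D is also blank at T0; that is a separate matter, and filling it would not close the gap between T1 and T3.
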